#### **11.1.3 Blinding Procedures**

This clinical trial is designed as a single-blind study. Single blind means that the subjects taking part in the study will not know whether they have been assigned to the investigational vaccine arm or the control arm. However, unlike a double blind study, here the Investigators, investigator staff, persons performing the assessments, and data analysts will not remain blind to the identity of the vaccine.

The Sponsor /designee will provide lists of participant numbers with vaccine group assignments to the site Investigator at each of the sites (i.e., unblinded list or randomisation list). The Investigator or his/her designee will use these lists to sequentially assign participants into study groups as they are enrolled. The site Investigator will work with the site staff member and design a strategy whereby this information is not inadvertently disclosed to the study subjects. The vaccine group assignment numbers will be entered on the CRF or source documents.

To facilitate auditing of vaccine administration, the subject number of the participant receiving a vaccine dose with date of injection/vaccination will be reported on to the vaccine box and vaccine

*Information contained in this publication is the property of EVI and ICGEB and is confidential and will not be disclosed to third parties without written authorization from EVI and ICGEB. No part of this document may be reproduced, stored in a retrieval system or transmitted in any form or by any means -electronic, mechanical, recording or otherwise - without the prior authorization of EVI and ICGEB*

[figure not shown][figure not shown]

vial. All vaccine boxes (containing used vials) will be saved for audit by the site and once the vaccine accountability is done these will be returned to sponsor or destroyed at site maintaining appropriate documentation. Study statisticians will be unblinded to study group identification for the purposes of performing the primary and secondary statistical analyses.

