### 4.4 Randomisation

A total of 45 healthy subjects in the age group of 18 to 45 years will be enrolled in the study. There will be three (3) cohorts in this study such that each cohort will consist of 15 eligible subjects randomised in a ratio of 2:1 to receive the particular dosage of investigational vaccine i.e. JAIVAC-1 – Montanide ISA 720 (10 subjects) and the control vaccine i.e. Hepatitis B vaccine (5 subjects) respectively, both administered as a 3-dose schedule. Thus, overall 30 subjects will receive JAIVAC-1 – Montanide ISA 720 (10 subjects for each cohort) and 15 subjects will receive control vaccine, Hepatitis B vaccine (5 subjects for each cohort).

Subjects will be randomised to study cohort using a reproducible, computer-generated permuted block randomisation schedule which will be cohort specific to ensure allocation ratio 2: 1 between investigational and control vaccine. Randomisation list will be generated and sent to DLS pharmacist for labelling and packaging purpose.

The randomisation number will be a three-digit subject number and will be cohort specific. The first digit identifies cohort as 1 (Cohort 1), 2 (Cohort 2) or 3 (Cohort 3), and the next two digits identify the subject within cohort and will be assigned sequentially as per the enrolment. Thus, study subjects in Cohort 1 will get randomisation numbers like 101, 102 and so on sequentially, study subjects in Cohort 2 will get randomisation numbers like 201, 202 and so on sequentially and study subjects in Cohort 3 will get randomisation numbers like 301, 302 and so on sequentially.

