10E3/ $\mu$ L, platelet count 150 to 500  $\times$  10E3/ $\mu$ L, Neutrophils 40 to 75 % or Eosinophils > 10 %, Sodium 136 to 145 mEq/L, Potassium 3.5 to 5.1 mEq/L, Random Blood Glucose 45 to 130 mg/dl and Alkaline Phosphatase 40 to 129 U/L (Appendix B and B-1).

11. Subjects with other clinically significant abnormal laboratory values based on the normal reference range (Refer Appendix B and B1) apart from the laboratory parameters listed above.
12. Subject with positive HIV, HBV or HCV test
13. Subject with positive direct Coomb's test
14. Subject with a peripheral blood film/smear with features of haemolysis or any other haematological disorder
15. Subject unable to give written informed consent
16. Subject unable to be closely followed for social, geographic or psychological reasons
17. Subject with previous history of drug or alcohol abuse interfering with normal social function during a period of one year prior to enrolment in the study or positive urine drug test
18. Subject with an abnormal 12-lead ECG at screening associated with relevant clinical symptoms/signs suggestive of cardiac pathology (including conduction disturbances)
19. Subject with an abnormal Chest X-Ray associated with relevant clinical symptoms/signs of respiratory pathology at screening/ anytime in the past 6 months
20. Subject with known history of congenital/hereditary immunodeficiency disorders
21. Subject with acute or chronic pulmonary, reticulo-endothelial, cardiovascular, hepatic, renal or neurological condition, or any other clinical findings that in the opinion of the clinical investigator, may increase the risk of participating in the study
22. Subject with any other condition that in the opinion of the clinical investigator would jeopardise the safety or rights of a participant in the trial or would render the participant unable to comply with the protocol

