### **6.4.4 Adherence to Randomisation List**

The Investigator will designate separate appropriately qualified personnel as the “vaccine manager” and the “vaccinator” respectively. The vaccine manager will be a qualified and trained individual, who will be exclusively dedicated to vaccine preparation while the “vaccinator” will be an independent physician/nurse, who will be responsible for administration of the assigned vaccine as indicated in the randomisation list for the individual subject.

*Information contained in this publication is the property of EVI and ICGEB and is confidential and will not be disclosed to third parties without written authorization from EVI and ICGEB. No part of this document may be reproduced, stored in a retrieval system or transmitted in any form or by any means -electronic, mechanical, recording or otherwise - without the prior authorization of EVI and ICGEB*

[figure not shown][figure not shown]

Only the subject will be blinded during the conduct of this single-blind study. Since the study and control vaccines can be distinguished by their appearance, the vaccine preparation area and the vaccine administration area will be physically separated. Also, the syringe barrels will be covered with opaque tape to ensure subject blinding.

Adherence to randomisation list will be verified by the study monitor by checking the randomisation list against the study vaccine administration records at each study visit.

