### **Randomisation Number**

A subject will be randomised into the study and assigned a unique randomisation number only after completion of an eligibility check of a subject's inclusion/exclusion criteria by the Investigator. The subject will be recognised by the randomisation number for all study-related assessments and procedures.

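### The enrolling Investigator holds the open randomisation list, so the next allocation is foreseeable and selection into the vaccine and control arms is possible

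*Supplement*

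**What the plan says.** On the list itself, section 11.1.3 states: "The Sponsor /designee will provide lists of participant numbers with vaccine group assignments to the site Investigator at each of the sites". It calls this the unblinded or randomisation list. The next sentence is: "The Investigator or his/her designee will use these lists to sequentially assign participants into study groups as they are enrolled". The only protection named is that the site should "design a strategy whereby this information is not inadvertently disclosed to the study subjects"; nothing shields the list from the people who enrol.

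Other sections bear on the point:

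- Section 4.4 specifies a "computer-generated permuted block randomisation schedule which will be cohort specific", in a 2:1 ratio, with numbers given in order of enrolment. The block size is not stated. The list also goes to the DLS pharmacist for labelling and packaging.
- Section 7.4.2 (Randomisation Number) has the subject "assigned a unique randomisation number only after completion of an eligibility check of a subject's inclusion/exclusion criteria by the Investigator".
- Section 5.4.2, exclusion 22, removes a volunteer with "any other condition that in the opinion of the clinical investigator would jeopardise the safety or rights of a participant in the trial". Exclusion 21 also ends in the investigator's opinion.
- Section 5.4 requires that all who meet the criteria be offered enrolment and forbids further exclusions.
- Section 5.3 replaces subjects who leave before the first vaccination. Section 11.3.1 counts in the ITT population only those who received a dose.
- Section 6.2 has packs prepared in advance from the randomisation list. Vials carry an unblinded label that may show the randomisation number, and the Investigator has access to storage.
- Section 6.4.4 appoints a vaccine manager "who will be exclusively dedicated to vaccine preparation" and a separate vaccinator. Neither role is given custody of the allocation at enrolment.

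**The concern.** Blinding and allocation concealment are separate safeguards. A trial can be open to its staff after assignment and still keep the next assignment from the person who decides who enters. Here the person who judges eligibility also holds the list. A volunteer who seems frailer, or less likely to complete the diary and visits, could be moved to a different place in the sequence or turned away, with the arm of that place in view.

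At stake is the second primary objective in section 3.1, the safety comparison with hepatitis B vaccine. Randomisation supports that comparison only if entry cannot depend on the coming allocation. Investigators stay unblinded and judge causality themselves, so concealing the allocation is one of the few protections still available. With arms of 10 and 5, the demographic comparison in section 11.5.1.1 could not be relied on to reveal an imbalance caused by selection.

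**Working it through.** The protocol offers no sample-size or predictability figure to reproduce. The check has four steps.

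**1. What is known, and when.** The list ties numbers to arms, not people to arms.

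- At Visit 2 (Day -14 to -1, section 7.4.3.2) eligibility is first judged, but a volunteer's place in the sequence is not yet fixed.
- At Visit 3 (section 7.4.3.3) the criteria are rechecked, the number is assigned and the first dose is given. By then the arm of the next number is known to the list-holder.

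Three routes for selection follow:

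- the order in which eligible men are enrolled on Day 0, which no section fixes;
- exclusions 21 and 22 at the Day 0 recheck;
- withdrawal after the number is assigned but before injection. Section 5.3 then replaces the subject, and section 11.3.1 drops him from the ITT population.

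**2. Arm sizes** (sections 4.4 and 5.3). 3 × 10 = 30 vaccine; 3 × 5 = 15 control; total 45; ratio 2:1. This agrees with the plan.

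**3. Weight of one subject.** The shift in an event proportion is 1/n.

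- Vaccine arm of one cohort: 1/10 = 10 percentage points.
- Controls of one cohort: 1/5 = 20 points.
- All controls pooled: 1/15 = 6.7 points.

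For scale, the exact 95% upper limit when no events are seen is 1 − 0.025^(1/n): 30.8% for n = 10, 52.2% for n = 5 and 21.8% for n = 15.

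**4. Predictability.** With the list in hand, 15 of 15 allocations per cohort are known beforehand. The comparison is a withheld list, with past allocations still known. Block size is not stated, so four schemes are assumed, and the guesser is assumed to know the scheme.

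In a block of *a* vaccine and *b* control places, the places known with certainty are those in the final run, whose expected length is a/(b+1) + b/(a+1). Expected correct guesses under the best strategy follow G(a,b) = max(a,b)/(a+b) + [a/(a+b)]·G(a−1,b) + [b/(a+b)]·G(a,b−1). For example, G(2,1) = 2/3 + (2/3)(1.5) + (1/3)(2) = 2.33, and five such blocks give 11.7.

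| Assumed blocks | Known with certainty, of 15 | Best guesses correct, of 15 |
|---|---|---|
| Five of 3 | 5 × (2/2 + 1/3) = 6.7 (44%) | 11.7 |
| 6 + 6 + 3 | 2 × (4/3 + 2/5) + (2/2 + 1/3) = 4.8 (32%) | 11.3 |
| 9 + 6 | (6/4 + 3/7) + (4/3 + 2/5) = 3.7 (24%) | 11.0 |
| One of 15 | 10/6 + 5/11 = 2.1 (14%) | 10.6 |
| Open list, as planned | 15 (100%) | 15 |

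Always guessing vaccine gives 10 of 15, so one concealed block of 15 leaves little to gain from prediction.

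**The case against.** The case for leaving the text alone has substance.

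- **Descriptive analysis.** Sections 11.1.1 and 11.5.1 set no hypothesis and say the sample is too small for group comparison, so no test is distorted.
- **Escalation.** The decision rests on DSMB review of Day 14 safety data from all 15 subjects of a cohort (section 8.2), not on a vaccine-control difference.
- **Limits on discretion.** Section 5.4 forbids added exclusions, most criteria in 5.4.2 are objective, and section 7.1 bars retesting of abnormal screening values.
- **Limits on opportunity.** Each cohort enrols over three days, numbers run in sequence, and the monitor checks administration against the list (section 6.4.4).

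This lowers the severity but does not remove the point. Exclusions 21 and 22 are listed criteria, so section 5.4 leaves them available. It also leaves the order of enrolment open. Swapping two men within three days breaks no stated rule and would still match the list when monitored. Assigning the number after the eligibility check does not help when the list is already in hand.

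A reader might infer that single-blinding is itself the fault, or that earlier allocations must also be hidden from the Investigator. The documents support neither. Sections 4.5 and 6.4.5 deliberately keep investigators and assessors unblinded after assignment, and hiding past allocations would contradict that design.

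**Conclusion.** The point holds as a weakness that should be fixed. As written, every next allocation is foreseeable to the enroller, and no concealment step appears anywhere in the protocol. Selection bias is therefore possible, and the harm is to the credibility of the vaccine-control safety comparison.

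The 10, 20 and 6.7 points are the weight of one subject, not an estimate of bias. The 20 points applies only if controls are reported by cohort; section 11.5.1 summarises by vaccine group and does not say whether the 15 controls are pooled. The predictability figures for a withheld list rest on assumed block sizes and a guesser who knows them.

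Stronger readings are tempting. One is that selection will occur, another that the escalation decisions are compromised, and a third that each man's arm is known when he is first screened. The documents show opportunity and no more; escalation uses the whole cohort; and a man's arm becomes foreseeable only when his place in the sequence is settled, essentially on Day 0.

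**What to change.** - **Section 11.1.3.** Replace the two sentences on the list. The list and the labelled packs are held only by the DLS pharmacist and the site vaccine manager, who takes no part in enrolment. The next number and its allocation are released only after the Investigator has signed the Visit 3 eligibility check and the subject is irrevocably enrolled.
- **Sections 4.4, 6.2, 6.4.4 and 11.1.3.** Align them on who holds the list and the packs. Withholding the list alone is not enough while section 6.2 gives the Investigator access to packs with unblinded labels.
- **Section 4.4.** Because investigators stay unblinded after assignment, use a block scheme not disclosed to the site, for example one 10:5 block per cohort or varying blocks. Earlier allocations need not be hidden.

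The roles are already in the plan, and no subjects or visits are added. The downside is a small change to site logistics: custody of the packs moves, and there is a release step on Day 0.

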## 11.2 Timing of Analysis

The data collected will be analysed at the end of the study i.e. after the last subject/last visit has been completed and the data has been locked. An interim analysis will be undertaken for data obtained till 28 days after the third dose of the vaccine for each dose-level (cohort). The details of the same will be stated in the SAP.

## 11.3 Definition of Analysis Sets

The Intention-To-Treat (ITT) population data set and the Per Protocol (PP) population data set will be used for the summarisation and descriptive analysis of the safety (primary endpoints) and immunogenicity data (secondary endpoints) as follows:

### 11.3.1 Intention-To-Treat Population (ITT Population)

The ITT population will include all randomised subjects who received at least one dose of either of the assigned study vaccines. This population will be used for reactogenicity, overall safety and immunogenicity analysis.

### 11.3.2 Per Protocol Population (PP Population)

The “Per Protocol” (PP) set includes the subjects from the ITT set who are compliant with the protocol. The PP analysis set will include all subjects who:

1. Received the randomised vaccine via intramuscular route
2. Met all eligibility (inclusion/exclusion) criteria; and
3. Developed no premature discontinuation criteria during the follow-up visits post vaccination
4. Did not take any prohibited concomitant medication during the vaccine period (up to Day 208)

This population will be used for reactogenicity and immunogenicity analysis.

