13. **Urine Drug Screen:** Urinalysis to test for drugs of abuse (benzodiazepines, opioids, amphetamine, cocaine, and THC) will be undertaken once at the Screening Visit (Visit 2) and subsequently on D28, D180 and D365. If the subject tests positive during screening period, he will be excluded from the study. If the subject tests positive on D28, D180 or D365, he will be immediately discontinued from the study.
14. **Randomisation Number:** Subjects, who fulfill all the eligibility criteria, will be randomised into the study with the assignment of a unique randomisation number.
15. **Diary Cards:** A pre-printed diary card will be given to the subject with detailed completion instructions on the day of vaccine administration and will be collected on Day 28 after each dose of vaccine. This diary card will be used for the record of solicited AEs (Day 0 through Day 14) and unsolicited AEs (Day 0 through Day 28). Thus three (3) such diary cards will be given to each subject. The Investigator will collect, review and transcribe the data from diary cards to CRF at pre-defined time-points.
16. **Record Immediate Reactogenicity:** Following vaccination on Days 0, 28 and 180, all subjects will be monitored at the site every 30 minutes till 3 hours for any immediate reactions with special emphasis on allergic/anaphylactic reactions. Vital signs will be done after the subject has been resting quietly for at least 5 minutes. BP will be taken in the supine position.
17. **Record Solicited AEs:** Each subject will record solicited AEs from vaccination through Day 14 after each dose on the diary card. These solicited AEs will be reviewed and transcribed from diary cards to CRF by the Investigator on Days 7, 14, 35, 42, 187 and 194. In addition, solicited AEs will be independently assessed by the investigator Days 14, 42 and 194 and the data directly entered in the CRF.
18. **Serology (ELISA and IFA):** Blood samples will be collected for serology assessment (ELISA and IFA) on Days 0, 28, 56, 180, 208 and 365. On Days 0, 28 and 180, blood samples will be collected prior to vaccination.
19. **Serology (IgG subclasses and GIA):** Blood samples will be collected for serology assessment (IgG subclasses by ELISA) on Days 0, 28, 56, 180, 208 and 365 and for GIA on Days 0, 56, 208 and 365 only. On Days 0, 28 and 180, blood samples will be collected prior to vaccination.

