#### 5.4.4 Discontinuation Criteria for a Subject during the Study

A discontinuation occurs when an enrolled subject ceases participation in the study, regardless of the circumstances, prior to completion of the protocol. Subjects may voluntarily withdraw from the study for any reason at any time or, if necessary, the Investigator or Sponsor may withdraw a subject from the study to protect the health of that subject. Subjects will be considered withdrawn if they state an intention to withdraw, or fail to return for visits, or become lost to follow up for any other reason.

Thus, a study subject may be discontinued from participation in the study if:

- Subject withdraws consent
- Any adverse event (AE), laboratory abnormality, inter-current illness, or other medical condition or situation occurs such that continued participation in the study would not be in the best interest of the subject
- Non-compliance with protocol requirements (e.g. use of restricted medication, urine drug screen positive, not following dosing procedures, failure to make scheduled study visits in a timely fashion)
- Wrongly enrolled subject may be discontinued from the study based on the decision taken by the designated Medical and Safety Monitor in consultation with the Sponsor (as required).
- Any other reason (as applicable) as adjudged by the Principal Investigator

The Investigator must manage the premature discontinuation /withdrawal of a study subject as follows:

- The Investigator shall determine/verify the primary reason for a subject's discontinuation/premature withdrawal from the study and record this information on the CRF.
- For subjects who are lost to follow-up (i.e., those subjects whose status is unclear because they fail to appear for study visits without stating an intention to withdraw), the Investigator should show "due diligence" by documenting in the source documents steps taken to contact the subject, e.g., dates of telephone calls, registered letters, etc.
- Discontinuation must be reported to designated Medical and Safety Monitor and Sponsor Representative without delay if it is due to an adverse event.
- If a subject terminates prematurely from the study early, all efforts will be made to complete D365 procedures for the given subject.

*All subjects who receive one dose of the vaccine will be included in the safety analysis.*

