### **Urine Drug Screen**

Urinalysis to test for drugs of abuse (benzodiazepines, opioids, amphetamine, cocaine, and THC) will be undertaken at Visits 2, 6, 10 and 14

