#### **Check Discontinuation Criteria**

At Visits 4, 5, 6, 7, 8, 9, 10, 11, 12 and 13 the Investigator will check for development of the subject discontinuation criteria per section 5.4.4.

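### Per-protocol rule 3 has no time limit, so a discontinuation event after Day 208 can take a subject's earlier antibody results out of the PP set

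*Supplement*

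**What the plan says.** Section 11.3.2 builds the PP set from ITT subjects who satisfy four rules. Rule 3 requires that the subject "Developed no premature discontinuation criteria during the follow-up visits post vaccination". It names no last visit. Rule 4, on prohibited concomitant medication, ends at Day 208. Both rules select subjects; neither selects samples. The PP set serves reactogenicity and immunogenicity. The ITT set (11.3.1) also serves immunogenicity.

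The criteria are in Section 5.4.4, where "a study subject may be discontinued from participation in the study if" certain conditions arise. These include withdrawal of consent and non-compliance; use of restricted medication, missed or late visits and "urine drug screen positive, not following dosing procedures" are examples of non-compliance. The section also treats loss to follow-up as withdrawal, and places a discontinuation "prior to completion of the protocol". Section 5.6 keeps its medication restrictions in force until six months after the third dose, well beyond Day 208.

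On timing, Section 7.4.2 states: "At Visits 4, 5, 6, 7, 8, 9, 10, 11, 12 and 13 the Investigator will check for development of the subject discontinuation criteria". Visit 13 is Day 208. Tables 1 and 7 agree, and the Visit 14 list (7.4.3.14) has no such check. The urine screen, however, "will be undertaken at Visits 2, 6, 10 and 14", and Visit 14 is Day 365. Footnote 13 to Tables 1 and 7 adds: "If the subject tests positive on D28, D180 or D365, he will be immediately discontinued from the study".

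Section 11.2 plans a look before the end of follow-up: "An interim analysis will be undertaken for data obtained till 28 days after the third dose of the vaccine".

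**The concern.** A per-protocol set is meant to drop data that a deviation could have distorted. An event on Day 250 or Day 300 cannot alter an antibody level measured on Day 28, 56, 180 or 208. A subject-level rule with no end date drops those results all the same.

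The rule also works against its neighbour. Rule 4 limits its medication test to Day 208. Because use of restricted medication is itself a discontinuation criterion, and the restriction runs past Day 208, a subject can pass rule 4 and fail rule 3 for the same act.

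At stake are the PP geometric means and responder proportions at the time points that describe the primary and booster responses, in arms of 10 and 5. If PP results are reported at the interim analysis, the same Day 28 to 208 estimates could differ between the interim and final reports.

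**Working it through.** The protocol gives no figure for this point, so there is none to reproduce. The check compares the text and then sizes a loss.

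**Step 1: reach of rule 3 compared with rule 4.**

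| Event | Rule 3, read literally | Rule 4 |
|---|---|---|
| Restricted medication on Day 150 | fails | fails |
| Restricted medication on Day 300 | fails (5.4.4, 5.6) | passes |
| Consent withdrawn on Day 250 | fails (5.4.4; before completion) | not relevant |
| Positive urine screen at Day 365 | unclear (step 3) | not relevant |

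There are 365 − 208 = 157 days between Visits 13 and 14 with no scheduled visit, so late withdrawal or loss is a realistic route.

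**Step 2: analyses affected.** Section 11.5.1.4 lists six comparisons: Day 28 vs 0, 56 vs 0, 56 vs 28, 208 vs 56, 180 vs 56 and 365 vs 208. Five of the six use nothing collected after Day 208. A subject excluded for a later event leaves all six in the PP set and none of the earlier five in the ITT set.

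**Step 3: the Day 365 urine screen.** Footnote 13 makes a positive result a discontinuation. Section 7.4.2 and the visit tables end the check at Day 208. Section 5.4.4 says a subject may be discontinued, where the footnote says he will be, and it places discontinuation before protocol completion. That sits awkwardly with a result from the last visit. The text does not settle the matter.

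**Step 4: precision.** Arm sizes are from 11.1.1: 10 per test arm and 5 per control arm. The half-width of the 95% interval for a mean log concentration is t(0.975, n−1) × SD/√n.

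- n = 10: 0.715 SD
- n = 9: 0.769 SD; ratio 0.769/0.715 = 1.07, or 7% wider
- n = 8: 0.836 SD; ratio 0.836/0.715 = 1.17, or 17% wider
- n = 5: 1.242 SD
- n = 4: 1.591 SD; ratio 1.591/1.242 = 1.28, or 28% wider

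For responder proportions with every subject responding, the exact lower 95% limit falls from 69.2% (10/10) to 66.4% (9/9). If 8 of 10 respond, the PP figure becomes 8/9 (88.9%) or 7/9 (77.8%) instead of 80.0%, depending on who is lost.

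**Step 5: how often.** The documents give no rate for events after Day 208. Assuming a rate p per subject, the chance of at least one is 1 − (1 − p)^n.

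| Assumed p | One arm of 10 | All 45 subjects |
|---|---|---|
| 1% | 9.6% | 36.4% |
| 2% | 18.3% | 59.7% |
| 5% | 40.1% | 90.1% |

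**The case against.** The strongest defence is that rule 3 is put into practice through the check in Section 7.4.2. That check ends at Visit 13, so rule 3 would also end at Day 208, in line with rule 4. This is a possible reading, but 11.3.2 does not refer to the check, and the definitions in 5.4.4 have no visit limit. A withdrawal on Day 250 is premature by the protocol's own definition.

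A reader might infer that a positive urine screen at Day 365 certainly erases a subject's earlier antibody results. The documents do not support that. The word premature in rule 3 and the definition in 5.4.4 may spare an event found at the final visit. In any case nothing is erased, since ITT retains every sample. Nor is the trial over for him at that moment: safety and serology samples are taken at the same Visit 14.

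A reader might also infer that the interim and final PP estimates must differ. Section 11.2 does not say that the interim uses the PP set and leaves its details to the SAP. Section 10.2 determines protocol violations at the end of the study. The difference is possible, not established.

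It is also fair to say that excluding non-completers as whole subjects is a common PP convention, and that Section 11 is an outline with full detail due in an SAP that is not shown. Both points lower the severity. They do not resolve the mismatch between rules 3 and 4, because the protocol itself states the PP definition and, unlike 11.2 and 11.4, Section 11.3 does not defer it.

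**Conclusion.** The point holds as a minor one. On its literal wording, rule 3 takes valid Day 28 to 208 results out of the PP set for events that came after them, and it undoes rule 4's Day 208 cut-off for restricted medication. The effect of a Day 365 urine result on PP membership cannot be determined from the text.

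A single loss costs 7% in interval width in a test arm and 28% in a control arm; two losses in a test arm cost 17%. These figures assume an unchanged SD. The expected cost depends on an event rate that the documents do not give, and is zero if no such event occurs. Immunogenicity is a secondary endpoint, the analysis is descriptive with no hypothesis test, and the ITT analysis is unaffected, so no error rate or primary conclusion is at risk.

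**What to change.** Amend 11.3.2, and carry the wording into the SAP, in one of two ways:

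- define PP immunogenicity membership by time point, so that a subject contributes every sample taken before his first excluding deviation; or
- give rule 3 the same Day 208 cut-off as rule 4 for the Day 0 to 208 analyses.

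In either case, show the PP denominator at each visit. If PP results are to appear at the interim analysis, say so.

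Separately, reconcile footnote 13 of Tables 1 and 7 with Sections 7.4.2 and 5.4.4 on what a Day 365 urine result means. Which discontinuation rule stands is for the sponsor to decide; the statistical need is only that its effect on PP membership be stated.

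The cost is wording alone, plus tables in which the PP denominator can vary by visit. No visit, sample or subject is added.
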